**Fig. 2 Fig2:**
[figure not shown]
Timeline for patients in the REPAIR-trial

### Surgical techniques

Prior to the start of the trial, a cadaver session will be held in order to standardize the technique of ACL repair and ACL reconstruction for all surgeons and to minimize the learning curve. All surgeons have extensive experience with ACL reconstruction and two out of five participating centers have experience with ACL repair.

The surgical technique of arthroscopic ACL repair has been more extensively described in the literature [39, 43, 55]. In brief, first the native torn ACL will be sutured with a loop using FiberWire sutures and advanced with one to two passes, so that the sutures exit the avulsed ligament towards the femur. Then, a small tunnel will be drilled from the native femoral insertion towards the lateral epicondyle using an ACL drill guide. The sutures will be passed through a TightRope button along with an additional FiberTape. The sutures and TightRope will be passed through the femoral tunnel and the button will be flipped. Then, a small tunnel will be drilled through the tibia from the anteromedial cortex towards the anterior part of the tibial footprint, and the FiberTape will be channeled through the tibial tunnel and, after cycling the knee, the FiberTape is fixed into the anteromedial cortex using a suture anchor at full extension. Finally, the repair sutures will be tensioned and tied in order to reapproximate the ACL towards the femoral footprint at 90° flexion.

For ACL reconstruction, a standard all-inside autograft hamstring tendon anatomic reconstruction technique is used [56, 57]. First, autologous hamstrings (semitendinosus and gracilis tendon) are harvested to the preference of the surgeon and will be prepared for graft usage with a minimum graft diameter of 8 mm [58, 59]. Then, femoral and tibial sockets are independently drilled in retrograde fashion using a FlipCutter drill. The graft is placed into the sockets, the knee is cycled in order to achieve optimal tension of the graft, and the graft is then fixed at the femoral and tibial side using a cortical button.

### Rehabilitation

Both treatment arms undergo the same rehabilitation program and consists of a milestone-based program according to the Dutch national guidelines for rehabilitation following ACL reconstruction and consists of three phases [60–62]. The first phase focuses on controlling swelling, restoration of range of motion and return of quadriceps muscle control, and generally takes 4 to 8 weeks. The second phase focuses on resuming light sporting activities and work without symptoms, and phase three focuses on full return to sports activities and heavy work. In case of meniscus repair, the first 6 weeks patients are partial weight bearing, range of motion is restricted to 0-90° and patients are not allowed deep bending or squatting for 4 months. Although the rehabilitation is milestone based and no strict time goals can be set, generally cycling on a stationary bike is allowed at 4-6 weeks, running at 10-12 weeks and return to sports and pivoting activities at a minimum of 9 months postoperatively.

### Blinding

Blinding for patients is not possible due to different scars, different postoperative radiographs and practical reasons. However, the data analysis will be performed in blinded fashion.

### Primary outcomes/endpoint (Table 2)

The primary outcome of this non-inferiority RCT is the subjective patient reported outcome (PROM) at two-year follow-up consisting of the subjective IKDC score [63] (Dutch validation [64]), as to a recent RCT on a similar topic [65, 66]. The primary endpoint is the subjective IKDC at two-years postoperatively. Patients will ultimately be followed for 10 years.

**Table 2 Tab2:** This chart provides an overview of which outcomes are collected at the different follow-up visits

	Pre	3 mns	6 mns	9 mns	1 yr	2 yrs	5 yrs	10 yrs
**Primary outcomes**								
IKDC subjective	X	X	X	X	X	X	X	X
**Secondary outcomes**								
KOOS	X	X	X	X	X	X	X	X
Lysholm	X	X	X	X	X	X	X	X
Forgotten Joint Score	X	X	X	X	X	X	X	X
Satisfaction & pain	X	X	X	X	X	X	X	X
Failure		X	X	X	X	X	X	X
Reoperation		X	X	X	X	X	X	X
Contralateral injury	X	X	X	X	X	X	X	X
IKDC objective	X	X	X	X	X	X	X	X
KT-1000	X	X	X	X	X	X	X	X
Return to sports		X	X	X	X	X	X	X
Tegner score	X	X	X	X	X	X	X	X
ACL-RSI		X	X	X	X	X	X	X
Osteoarthritis (X-ray)	X							X
AE, SAE, SUSAR	X	X	X	X	X	X	X	X

*IKDC* indicates International Knee Documentation Committee, *KOOS* Knee Injury and Osteoarthritis Outcome Score, *AE* adverse events, *SAE* serious adverse event, *SUSAR* Suspected Unexpected Serious Adverse Reaction, *Pre* preoperatively, *mns* months, *yr(s)* year(s)

### Secondary outcomes (Table 2)

The secondary outcomes of this RCT are fourfold and consist of (I) other subjective outcomes, (II) objective outcomes, (III) return to sports, and (IV) long-term osteoarthritis.

Other collected PROMs for this study are the Knee Injury and Osteoarthritis Outcome Score (KOOS) [67] (Dutch validation [68]), Lysholm score [69] (Dutch validation [70]), and Forgotten Joint Score (FJS) [28] (Dutch validation [71]). Furthermore, patient satisfaction and pain scores are collected using a numeric rating scale (range 0 – 10).

The objective outcomes consist of failure of ACL repair/graft, reoperation, contralateral injury, and laxity. Failure is defined as a (traumatic) rerupture or symptomatic instability with activities. Reoperation is defined as any new operation on the same knee for any other reason than revision (e.g., symptomatic meniscus tear, hardware irritation, infection or stiffness/arthrofibrosis). Contralateral injury was defined as a complete ACL rupture of the contralateral ACL. Stability is defined as the laxity found with physical examination using the IKDC objective score form [72], which includes the Lachman, anterior drawer and pivot shift test, and side-to-side differences is assessed using KT-2000 or Rollimeter.

Return to sports is defined as (I) returning to sports, (II) returning to the same sport, and (III) returning to the preinjury level of sport. The preinjury and postoperative Tegner activity scale are also collected, which enables comparison with other studies [73] (Dutch validation [70]). Finally, confidence of return to sports and fear of reinjury are assessed using the ACL-Return to Sports Index (ACL-RSI) score [74] (Dutch validation [75]).

Osteoarthritis will be reviewed at 10-year follow-up. Radiographs of both knees will be performed, and the operated knee will be compared to (I) the contralateral knee if no operation occurred in that knee, and (II) the ipsilateral knee radiograph preoperatively. The Kellgren-Lawrence (KL) grade will be used to assess the incidence and grades of osteoarthritis.

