**Methods:**

This study is a multicenter prospective block randomized controlled trial. A total of 74 patients with acute proximal isolated ACL tears will be assigned in a 1:1 allocation ratio to either (I) ACL repair using cortical button fixation and additional suture augmentation or (II) ACL reconstruction using an all-inside autologous hamstring graft technique. The primary objective is to assess if ACL repair is non-inferior to ACL reconstruction regarding the subjective International Knee Documentation Committee (IKDC) score at two-years postoperatively. The secondary objectives are to assess if ACL repair is non-inferior with regards to (I) other patient-reported outcomes measures (i.e. Knee Injury and Osteoarthritis Outcome Score, Lysholm score, Forgotten Joint Score, patient satisfaction and pain), (II) objective outcome measures (i.e. failure of repair or graft defined as rerupture or symptomatic instability, reoperation, contralateral injury, and stability using the objective IKDC score and Rollimeter/KT-2000), (III) return to sports assessed by Tegner activity score and the ACL-Return to Sports Index at two-year follow-up, and (IV) long-term osteoarthritis at 10-year follow-up.

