**Pre-operative**	
Complete primary ACL tear on physical examination and MRI	Complete ipsilateral concomitant knee ligament injury requiring surgery
Tear in proximal quarter on MRI [50, 51]	Concomitant ipsilateral knee dislocation or patellar dislocation
Age 18 – 50 years [22, 52]	Osteoarthritis KL grade ≥ 2
Preinjury Tegner level ≥ 5 & desired Tegner level ≥ 5 [53]	Previous ipsilateral ACL reconstruction/repair
Operation within 4 weeks of injury [54]	Intra-articular corticosteroids 6 months prior
	No understanding of Dutch language or not capable of understanding the study and participation
	No preoperative flexion of 90 degrees
	Grade 3 pivot shift indicating gross ligament instability that requires additional procedures
	Gross lower leg malalignment requiring bony osteotomies
	Muscular, neurological or vascular diseases that influence rehabilitation or surgery
	Prolonged use medication use of prednison or cytostatics
	Pregnancy during injury or surgery
	Osteoporosis that influence rehabilitation or surgery

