### Statistical analysis

Both an intention to treat analysis and per protocol analysis will be performed for this non-inferiority study. Comparison of nominal variables between ACL repair and ACL reconstruction will be performed using two-by-two tables with Pearson’s Chi-square test or Fisher’s exact test (in case one of the cells is < 5). For comparison of continuous variables, first tests for normal distribution of values are performed and independent t-tests are used of normal distributed values and non-parametric t-tests are used for not-normally distributed values.

A mixed model analysis for repeated measures will be performed to assess differences between both groups. Furthermore, a multivariate regression analysis will be performed for the primary endpoint of IKDC at two-years follow-up in order to correct for potential confounders. Statistical analysis will be performed using SPSS version 25.0 (IBM Software, Armonk, NY, USA). All tests are two-sided and a *p*-value of < 0.05 is considered statistically significant.

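### 10-year osteoarthritis: the named comparisons are within patient, one is limited by a largely post-randomisation event, and no margin supports the non-inferiority objective

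*Protocol article*

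**What the plan says.** The Methods paragraph of the abstract introduces the secondary aims with "The secondary objectives are to assess if ACL repair is non-inferior with regards to" and lists as the last of them "IV) long-term osteoarthritis at 10-year follow-up". That is a question about one arm against the other.

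The section Secondary outcomes (Table 2) then gives two reference films for the operated knee. For the first, "the operated knee will be compared to (I) the contralateral knee if no operation occurred in that knee". The other is "II) the ipsilateral knee radiograph preoperatively", with no condition attached. It adds: "The Kellgren-Lawrence (KL) grade will be used to assess the incidence and grades of osteoarthritis". Table 2 schedules the radiograph before surgery and at 10 years.

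Table 1 excludes patients with "Osteoarthritis KL grade ≥ 2" at entry. The Statistical analysis section says: "Comparison of nominal variables between ACL repair and ACL reconstruction will be performed using two-by-two tables", by chi-square or Fisher's exact test. All tests there are two-sided with a 0.05 threshold. The only non-inferiority limit in the article is 8.8 points on the subjective IKDC score, in the Sample size section.

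**The concern.** Three features do not fit together.

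- The objective concerns the difference between arms, but each named osteoarthritis comparison is inside one patient. The article does not say which quantity is to be carried into a between-arm contrast.
- The contralateral comparison applies only to patients whose other knee was not operated on. Over 10 years that status is decided largely after randomisation, and contralateral ACL rupture is itself a listed trial outcome. If the arms differ in who has such an operation, comparing them on this measure no longer compares the groups that were randomised.
- Non-inferiority needs a margin and an interval to set against it. For osteoarthritis the article gives no margin, and its test can only detect a difference. With so few patients, a non-significant result is likely even if one arm does materially worse, and it could be reported as meeting the objective.

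At stake is a long-term joint-health claim for repair that the data could not carry.

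**Working it through.** **1. The plan's own figure.** Inputs from the Sample size section: margin 8.8, SD 11, two-sided alpha 0.05 (0.025 in the non-inferiority direction), power 90%, loss 10%.

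n per arm = 2 × (1.960 + 1.282)² × 11² / 8.8² = 2 × 10.51 × 1.5625 ≈ 32.8, so 33. Allowing for loss, 33 / 0.90 = 36.7, so 37 per arm and 74 in total. This reproduces the stated size. It rests on the IKDC score and takes no account of osteoarthritis.

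**2. Who is in each osteoarthritis measure.**

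| Measure | Condition stated | Patient with contralateral operation |
|---|---|---|
| Operated vs contralateral knee | Contralateral knee not operated on | Left out |
| Operated knee, 10 years vs preoperative | None | Included |
| KL incidence and grade | None | Included |

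Table 1 bars previous ACL surgery on the ipsilateral side only, so some contralateral operations may precede entry. The restriction is therefore largely, not wholly, post-randomisation.

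The article gives no rate of contralateral surgery. If it were 5% to 15% (assumption), 0.05 × 74 = 3.7 to 0.15 × 74 = 11.1, or about 4 to 11 patients, would have no contralateral comparison. They would keep the other two measures.

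**3. Precision of a between-arm comparison.** Assumptions: equal incidence p of new KL grade 2 or higher in both arms; 33 evaluable per arm (the plan's 10% loss) down to 25 (heavier loss by 10 years). The normal approximation is:

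half-width = 1.96 × √(2p(1 − p)/n)

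- p = 0.20, n = 33: 1.96 × √(0.32/33) = 0.193
- p = 0.20, n = 30: 1.96 × √(0.32/30) = 0.202
- p = 0.20, n = 25: 1.96 × √(0.32/25) = 0.222
- n = 33, p from 0.10 to 0.40: 0.145 to 0.236

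**4. What that means for non-inferiority.** Even with an observed difference of exactly zero, at 20% incidence the upper confidence limit would lie 19 to 22 points above zero. Non-inferiority could then be declared only with a margin at least that wide, which would tolerate about 39% to 42% against 20%, roughly a doubling. For 80% or 90% power with 33 per arm, the margin would have to be (1.96 + 0.8416) × 0.0985 = 0.276 or (1.96 + 1.2816) × 0.0985 = 0.319.

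**5. What is already available.** Because KL grade 2 or higher is excluded at entry, that grade in the operated knee at 10 years is new disease in every patient. It needs no contralateral reference and no exclusion.

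**The case against.** The strongest reply is that the outcomes section describes measurement, not analysis. A side-to-side difference or a change from baseline is one value per patient, and such values can be compared between arms. Laxity in the same section is also a side-to-side measure, and no one would say it cannot be compared by arm. KL incidence is named as an outcome, the Statistical analysis section supplies a general between-arm test, and both intention-to-treat and per-protocol analyses are planned. The two-by-two tables are assigned to nominal variables, so KL grades are not necessarily forced into them; the non-parametric tests in the same paragraph could be used. Restricting the contralateral comparison has a sensible reason, since an operated knee is a poor healthy reference. An article may also leave the margin and model to a fuller document.

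Much of this stands, and it rules out two stronger readings that a reader might infer:

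- **That patients with contralateral surgery are dropped from the osteoarthritis outcome.** They are not. The condition belongs to the contralateral comparison alone.
- **That the plan cannot answer the between-arm question at all.** It can, through KL incidence and the general test.

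Two things survive the reply. A between-arm contrast of the contralateral comparison would still be made in a subset selected largely after randomisation. And the article itself states a non-inferiority objective for osteoarthritis alongside two-sided difference tests. A margin held in another document would not cure the imprecision shown above. The wide interval applies under any osteoarthritis definition, so it is an argument against the non-inferiority claim, not against the choice of comparisons.

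**Conclusion.** The point holds in a limited form. The osteoarthritis comparisons named are within patient, and one is restricted by a largely post-randomisation event. The stated non-inferiority objective has neither a margin nor a suitable test in this document. A non-inferiority conclusion drawn from a non-significant two-sided test would be unsound.

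The size of the problem rests on assumed rates, because the article gives none: about 19 to 22 percentage points of half-width at 20% incidence with 33 down to 25 patients per arm, and 14 to 24 points at 33 per arm as incidence runs from 10% to 40%.

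This is a modest matter on a 10-year secondary outcome. The primary endpoint, the sample size of 74 and the two-year results are not affected.

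**What to change.** - Define the main osteoarthritis analysis as a between-arm comparison of operated-knee KL grade at 10 years, in all randomised patients with a film, using an ordinal model adjusted for preoperative KL grade. That grade is already collected and can only be below 2.
- Report alongside it the risk difference for new KL grade 2 or higher, with a 95% CI.
- Keep the contralateral comparison as descriptive, and do not let it decide who enters the between-arm analysis.
- Reword the fourth secondary objective so that osteoarthritis is estimated with an interval and no non-inferiority conclusion is drawn.

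The cost is a change of wording. The same radiographs serve, and no visit or patient is added. The small downside is that the 10-year statement on osteoarthritis becomes an interval, probably a wide one, in place of a claim.

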### Sample size

The sample size calculation was based on the primary outcome of this study (subjective IKDC score), similar to another RCT design on this topic [65]. It has been shown that a difference of 8.8 points in the subjective IKDC score is the minimal clinically important difference (MCID) [76]. Using this non-inferiority limit of 8.8 points, and a standard deviation of 11 points [42, 65, 77] along with a two-sided alpha of 0.05, a power of 90%, and a lost-to-follow-up rate of 10%, a total of 37 patients in each group (74 patients in total) are needed to assess the primary outcome of this non-inferiority RCT. This sample size is also sufficient for the MCID of KOOS [78] and Lysholm score [79]. Given the recent studies that showed that 30-40% of the acute tears will have repairable proximal ACL tears [50, 80], we estimate that approximately 200 patients will be needed to be screened preoperatively to achieve the sample size of 74 patients [81].

### Statistical analysis

Both an intention to treat analysis and per protocol analysis will be performed for this non-inferiority study. Comparison of nominal variables between ACL repair and ACL reconstruction will be performed using two-by-two tables with Pearson’s Chi-square test or Fisher’s exact test (in case one of the cells is < 5). For comparison of continuous variables, first tests for normal distribution of values are performed and independent t-tests are used of normal distributed values and non-parametric t-tests are used for not-normally distributed values.

A mixed model analysis for repeated measures will be performed to assess differences between both groups. Furthermore, a multivariate regression analysis will be performed for the primary endpoint of IKDC at two-years follow-up in order to correct for potential confounders. Statistical analysis will be performed using SPSS version 25.0 (IBM Software, Armonk, NY, USA). All tests are two-sided and a *p*-value of < 0.05 is considered statistically significant.

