### Study design

This study is a multicenter prospective RCT with randomization into two treatment arms: (I) arthroscopic ACL repair with suture augmentation and (II) arthroscopic ACL reconstruction surgery. This study is a non-inferiority study with the hypothesis that arthroscopic ACL repair is non-inferior to (equivalent or better than) arthroscopic ACL reconstruction. All patients with proximal tears will be randomized during the operation into one of these treatment arms and will be followed up to 10-years postoperatively.

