### Study sample

Potential candidates will be selected from five participating orthopaedic surgery departments, of which one is an academic hospital, three are teaching hospitals and one is a private hospital. Inclusion and exclusion criteria for participation in the study are displayed in Table 1. In general, potential inclusion involves all patients with acute, isolated, complete, proximal ACL tears that have a desire to return to pre-injury activities and exclusion involves all concomitant ligamentous and osteoarthritic injuries and skeletally immature patients. A flowchart of the study is shown in Fig. 1. Patients can withdraw their participation in this study at any time point, at which their data will be deleted.

**Table 1 Tab1:** Inclusion and exclusion criteria for participating in this trial

Inclusion criteria	Exclusion criteria

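### Failure, reoperation and contralateral injury are collected to 10 years, but the only method that applies to them is a two-by-two table, which ignores follow-up time at 5 and 10 years

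*Protocol article*

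**What the plan says.** Under Secondary outcomes, the protocol article lists these event outcomes: "The objective outcomes consist of failure of ACL repair/graft, reoperation, contralateral injury, and laxity". Its failure definition describes something that can happen at any moment after surgery: "Failure is defined as a (traumatic) rerupture or symptomatic instability with activities". Under Study design, patients "will be followed up to 10-years postoperatively".

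Table 2, described as an "overview of which outcomes are collected at the different follow-up visits", marks failure, reoperation and contralateral injury at all seven postoperative visits: 3, 6 and 9 months, and 1, 2, 5 and 10 years.

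Statistical analysis assigns methods by type of variable. For yes/no outcomes it says: "Comparison of nominal variables between ACL repair and ACL reconstruction will be performed using two-by-two tables", tested by Pearson's chi-square or Fisher's exact test. The section also states: "A mixed model analysis for repeated measures will be performed to assess differences between both groups". That sentence is not linked to the three event outcomes. The multivariable regression is confined to the 2-year IKDC score. No time-to-event method is named.

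Two other statements bear on the point. Sample size allows for 10% loss to follow-up. Study sample says: "Patients can withdraw their participation in this study at any time point, at which their data will be deleted".

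**The concern.** A two-by-two table needs a yes or no for every patient at the chosen time. A patient who leaves event-free at year 3 has no known status at year 5 or 10. If that patient is kept as a non-failure, the denominator includes time that nobody observed and incidence is too low. If the patient is dropped, early failures stay in while event-free follow-up is discarded, and incidence is too high. The two rules err in opposite directions. If loss differs between the arms, each rule also creates an arm difference where none exists.

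Longer-term failure matters in this trial. The Background describes good early but disappointing mid-term results of open repair, and it quotes a national study group asking for long-term evidence. Failure is also among the outcomes on which non-inferiority is to be assessed. Patients know which operation they had (Blinding), so unequal loss between the arms is possible.

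**Working it through.** **The plan's own figure.** The sample size reproduces. With margin 8.8, SD 11, true difference 0, one-sided alpha 0.025 (two-sided 0.05) and power 90%:

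n per arm = 2 × 11² × (1.960 + 1.282)² / 8.8² = 32.8, so 33. Then 33 / 0.90 = 36.7, so 37 per arm and 74 in total.

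This is not in dispute. It supplies the 37 per arm used below.

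**Inputs for the failure check.**
- From the documents: failure of 6 to 9% in recent series of proximal repair (Background); 10% loss (Sample size).
- Assumed, because the documents give no value: true failure of 15% as a higher case; 20%, 30% or 40% loss by a late visit; constant hazards of failure and loss, independent of each other.

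**Formulas.** For true cumulative failure F and cumulative loss L at the time point:
- a = −ln(1 − F), b = −ln(1 − L), T = 1 − (1 − F)(1 − L)
- failures observed before loss: O = a/(a + b) × T
- lost event-free: C = b/(a + b) × T
- rule 1, lost counted as non-failure: O
- rule 2, lost event-free dropped: O / (1 − C)

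Under these assumptions a censoring-aware estimate targets F itself.

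**Worked example, F = 15%, L = 30%.** a = 0.1625, b = 0.3567, T = 1 − 0.85 × 0.70 = 0.405. O = 0.1625/0.5192 × 0.405 = 0.127. C = 0.3567/0.5192 × 0.405 = 0.278. Rule 1 gives 12.7%. Rule 2 gives 0.127/0.722 = 17.6%.

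| True failure | Loss | Rule 1 | Rule 2 |
|---|---|---|---|
| 6% | 10% | 5.7% | 6.3% |
| 9% | 10% | 8.5% | 9.5% |
| 15% | 10% | 14.3% | 15.7% |
| 9% | 20% | 8.1% | 10.0% |
| 9% | 30% | 7.6% | 10.6% |
| 9% | 40% | 7.1% | 11.5% |
| 15% | 20% | 13.5% | 16.5% |
| 15% | 30% | 12.7% | 17.6% |
| 15% | 40% | 11.8% | 18.8% |

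The 10% rows correspond to the planned loss at 2 years. Every error there is under 1 point.

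**Unequal loss, same true failure in both arms, 20% versus 40% loss.**
- True 15%: rule 1 shows 13.5% versus 11.8%, a false difference of about 1.7 points. Rule 2 shows 16.5% versus 18.8%, about 2.3 points the other way.
- True 9%: rule 1 shows 8.1% versus 7.1% (1.0 point). Rule 2 shows 10.0% versus 11.5% (1.5 points), again reversed.

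**Scale.** One patient in 37 is 1/37 = 2.7 points. The 95% half-width for a difference between two arms of 37 is 1.96 × √(2p(1 − p)/37): 13 points at p = 9% and 16 points at p = 15%, before any loss.

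**The case against.** The strongest reply is that the article nowhere commits to comparing failure by a two-by-two table at 5 or 10 years. Table 2 is a collection schedule, the primary endpoint is at 2 years, and the only outcome that the objectives expressly tie to the last visit is "long-term osteoarthritis at 10-year follow-up". At a fixed 2-year time point with modest loss, comparing proportions is a standard choice. That part stands, and the 2-year table is not criticised here. It does not settle the later visits: the outcomes are collected there, and no other named method is tied to them.

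It can also be said that the real gap is a rule for missing status, which an article commonly leaves to the full protocol or SAP. The missing rule alone would be no finding. The point is that the method actually stated takes no account of follow-up time. Imputing status is compatible with a two-by-two table, so dropping and counting as non-failure are the two usual rules but not the only ones.

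A third reply is that the biases are small and rest on assumed rates. This is right. The false arm differences above are all below one patient per arm and well inside sampling error.

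A reader might infer that the trial's verdict on repair, or its non-inferiority claim, is at risk. The documents do not support that: these outcomes are secondary, the primary endpoint is the 2-year IKDC score, and no scenario above shows a conclusion changing. A reader might also take late failure as the stated reason that repair was abandoned. The Background reports mid-term deterioration, but credits the abandonment ultimately to prospective comparisons favouring reconstruction, and it cites three recent studies with good results maintained at mid-term.

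Finally, Kaplan-Meier is no complete cure. Symptomatic instability may have no clear onset date, and after year 2 the visits are 3 and 5 years apart. Loss may be related to failure. Events in patients whose data are deleted at withdrawal cannot be recovered by any censoring method. All of this stands and shapes the fix.

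**Conclusion.** The point holds as a modest weakness in the analysis of three secondary outcomes. The stated method suits a 2-year comparison with about 10% loss, where the error is about 1 point or less. It suits 5- and 10-year event outcomes poorly: at 30% loss the reported rate is off by about 1.4 to 1.6 points if true failure is 9% (7.6% or 10.6%), and by 2.3 to 2.6 points if it is 15% (12.7% or 17.6%). The direction depends on how lost patients are counted.

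The late loss rates, the 15% failure rate, and the constant and independent hazards are assumptions. With 37 per arm, sampling error exceeds these biases. The case for change is that the bias is avoidable at little cost, not that it is large.

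**What to change.** Analyse failure, reoperation and contralateral injury as time from surgery to first event, censored at last contact. Report Kaplan-Meier cumulative incidence per arm at 2, 5 and 10 years, with the difference and its 95% confidence interval. Record event dates on the case report form. Where onset is known only to lie between two visits, as may be so for symptomatic instability, use the visit interval through a life-table or interval-censored estimate. Keep the 2-year two-by-two table as a sensitivity analysis and state its denominator.

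The cost is some analysis wording and a date field; no extra patients or visits are needed. Intervals will be wide because events are few, the estimates rely on independent censoring, and events removed when a withdrawn patient's data are deleted stay lost. The report should state these limits.

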### Goal and hypotheses

The goal of this multicenter non-inferior prospective randomized controlled trial is therefore to compare the outcomes of arthroscopic ACL repair with suture augmentation to ACL reconstruction for patients with proximal tears in a 1:1 allocation ratio. The primary outcome is the subjective International Knee Documentation Committee (IKDC) score and the secondary outcomes are other patient-reported outcomes, objective outcomes and return to sports. It is hypothesized that patients following ACL repair with suture augmentation have non-inferior primary and secondary outcomes when compared to ACL reconstruction due to the less invasive surgery.

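### None of the three analyses that can bear on two-year subjective IKDC is tied to the preoperative score, so the trial may give up some precision against its 8.8-point margin

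*Protocol article*

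**What the plan says.** The primary endpoint is subjective IKDC two years after surgery. Table 2 marks the same score at the preoperative visit and at all seven follow-up visits: "IKDC subjective X X X X X X X X".

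The Statistical analysis section then gives three methods that can apply to that endpoint:

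- For continuous variables in general, after a normality check, "independent t-tests are used of normal distributed values and non-parametric t-tests are used for not-normally distributed values".
- A mixed model for repeated measures to compare the groups. Its terms, and the role of the preoperative value, are not given.
- For the two-year score by name, "a multivariate regression analysis will be performed for the primary endpoint of IKDC at two-years follow-up in order to correct for potential confounders". The covariates are not listed.

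The section does not say which of the three decides non-inferiority, and it names preoperative IKDC in none of them. The Sample size section works from an unadjusted spread: "Using this non-inferiority limit of 8.8 points, and a standard deviation of 11 points", "along with a two-sided alpha of 0.05".

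**The concern.** The non-inferiority conclusion turns on one confidence limit for the two-year difference compared with 8.8 points, with about 33 evaluable patients per arm. A baseline measurement of the same score is often the most useful covariate for narrowing that interval, and here it is already scheduled. An unadjusted t-test or rank test ignores it: variation that baseline could explain stays in the error term, and a chance imbalance in preoperative IKDC stays in the estimate.

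The stated purpose of the regression is a second weakness. In a randomised comparison, baseline differences between arms arise by chance, so the reason to adjust is precision from prognostic variables fixed beforehand. Describing the purpose as correction for confounders invites a choice of covariates after imbalances have been seen, which is undesirable when the result is read against a margin.

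**Working it through.** **Inputs from the Sample size section:** margin 8.8, SD 11, two-sided alpha 0.05, power 90%, loss to follow-up 10%. Allocation is 1:1 (Goal and hypotheses). I take the true difference as 0.

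**Input not in the article:** the correlation ρ between preoperative and two-year IKDC. I use a range from 0 to 0.6.

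**Step 1: reproduce the plan's figure.** n per arm = 2(1.960 + 1.282)² × 11² / 8.8² = 32.8, so 33. Allowing for loss, 33 / 0.9 = 36.7, so 37 per arm and 74 in total. This matches the protocol and contains no baseline term.

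**Step 2: unadjusted analysis with 33 per arm.** The standard error is 11 × √(2/33) = 2.708. The normal approximation gives power 90.1%; the noncentral t with 64 degrees of freedom gives 89.3%. The 95% CI half-width is 1.998 × 2.708 = 5.41 points.

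**Step 3: adjustment for one baseline covariate.** The residual SD is 11√(1 − ρ²), with 63 degrees of freedom.

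| ρ (assumed) | Residual SD | Variance removed | Power | CI half-width |
|---|---|---|---|---|
| 0 | 11.00 | 0% | 89.3% | 5.41 |
| 0.2 | 10.78 | 4% | 90.4% | 5.30 |
| 0.3 | 10.49 | 9% | 91.8% | 5.16 |
| 0.4 | 10.08 | 16% | 93.7% | 4.96 |
| 0.5 | 9.53 | 25% | 95.9% | 4.69 |
| 0.6 | 8.80 | 36% | 97.9% | 4.33 |

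At ρ = 0.5 the gain is 6.6 percentage points, equivalent to 33 / (1 − 0.25) = 44 patients per arm analysed unadjusted. At ρ = 0.2 and 0.3 it is 1.1 and 2.5 points.

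**Step 4: the cost if baseline predicts nothing.** At ρ = 0 the lost degree of freedom costs about 0.01 percentage point of power. Step 3 ignores the small inflation from chance imbalance in the covariate, on average a factor of about 1 + 1/(66 − 4) = 1.016 on the variance. Including it, power is 88.8% at ρ = 0, 90.0% at 0.2, 91.4% at 0.3 and 95.6% at 0.5. The worst case is therefore about half a percentage point, and adjustment breaks even near ρ = √(1 − 1/1.016) ≈ 0.13.

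**The case against.** The strongest reply is that nothing here is wrong. The t-test sentence is a general rule for continuous variables and is not named as the primary analysis. The analysis tied by name to two-year IKDC is the regression, which is adjusted. If its covariates include preoperative IKDC, it is already an analysis of covariance. The mixed model could also use the preoperative score, as a covariate or as a response. Model terms and covariate lists are commonly left to a full protocol or analysis plan, which is not shown. An unadjusted comparison is valid in a randomised trial, and the sample size was built for one. Finally, the correlation is unknown, and Table 1 requires surgery within four weeks of injury, so the preoperative score reflects a freshly injured knee and may predict two-year function poorly.

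Most of this stands. A reader might infer that the unadjusted t-test is the primary analysis and that the trial therefore throws precision away, or that it is underpowered. The article supports neither: it is silent on baseline IKDC and does not exclude it, and its stated size follows from its own inputs.

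The reply does not remove what the section does state. It sets an unadjusted rule that covers the two-year score along with every other continuous variable, gives confounding as the reason for adjustment, and links no analysis to a baseline score that is already scheduled. The missing covariate list is not the point; the stated methods and the stated reason for adjusting can be improved.

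**Conclusion.** The point holds as an improvement of uncertain size, not as an error or a demonstrated loss. The trial meets its 90% target without adjustment by the normal formula (90.1%; 89.3% by the noncentral t). Under the plan's SD of 11, no true difference and 33 evaluable patients per arm, adjusting for preoperative IKDC would add about 1 percentage point of power at ρ = 0.2, 2.5 at 0.3 and 6.6 at 0.5, slightly less once chance covariate imbalance is counted. A gain above 5 points needs ρ of about 0.45 or more, and the article offers no evidence on ρ. The possible downside is about half a point.

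**What to change.** State that the primary non-inferiority analysis is the two-year difference between arms in subjective IKDC, with its 95% confidence interval, from one pre-specified model adjusted for preoperative IKDC as a continuous covariate. Either an analysis of covariance or the planned mixed model would serve; in the mixed model, enter the preoperative score as a covariate and take the two-year contrast. Compare the adjusted confidence limit with the 8.8-point margin.

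Keep the unadjusted t-test as a sensitivity analysis. Either drop the regression for confounders or fix its covariates in advance for prognostic value; preinjury Tegner level, already collected, is one candidate. The same baseline-adjusted form suits KOOS, Lysholm and the other scores that Table 2 schedules before surgery.

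The cost is wording only: no new patients, visits or data, one degree of freedom, and a simple rule such as mean imputation for any missing preoperative score.
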